### Sample size calculation

A power analysis was performed to estimate the required number of participants for the study. This calculation assumed that 30% of patients will continue using statins after the N=1-intervention compared with 12% in the usual care group and included a drop-out margin of 25%. We have based the assumption that 30% of patients will continue statin therapy in the N=1-intervention arm of the study on four previous N=1-studies conducted in patients with statin intolerance that assessed the proportion of patients who restarted or were willing to restart statin therapy.^13 14 23 24^ Two of these studies reported the lowest lower bounds of the 95% Confidence Intervals (95% CIs) for this outcome of 29%.^23 24^ To ensure a conservative estimate for our power calculation, we therefore based our assumption on this lower bound. We have also assumed that 12% of patients in the usual care arm will continue statin therapy, which we consider a cautious estimate. However, we anticipate that some contamination bias may occur, as physicians may apply insights gained from the N=1-intervention arm in routine care, for example, through improved communication regarding statin intolerance and nocebo effects. This could lead to a higher proportion of patients in the usual care arm choosing to continue treatment.

Based on a two-sided alpha level of 0.05 and 80% power, our calculation showed that a total of 247 participants are needed for the study that has a 2:1 ratio of participants in the intervention and control arms respectively. Our trial has been funded for 249 participants, so we will include this amount of participants.

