All HCPs who participate in this study will be trained to provide information on the nocebo effect to study participants. In this training, HCPs will receive practical tips focusing on communication about the nocebo effect. This training will be provided by the study coordinator (RM) and two dedicated behavioural psychologists involved in this project, one of which was also a patient advocate that was involved in the study.

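### The intervention-arm rate is said to rest on a 29% lower bound but 30% is used, and the anticipated contamination of usual care has no stated allowance; power is about 76% at 29% vs 12% and falls further if the usual-care rate exceeds 12%

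*Protocol article*

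**What the plan says.** All of this is in the protocol article, mainly under Sample size calculation.

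- Rates used: "This calculation assumed that 30% of patients will continue using statins after the N=1-intervention compared with 12% in the usual care group".
- Origin of the intervention rate: four earlier N=1 studies. "Two of these studies reported the lowest lower bounds of the 95% Confidence Intervals (95% CIs) for this outcome of 29" per cent. The section continues: "To ensure a conservative estimate for our power calculation, we therefore based our assumption on this lower bound".
- Usual-care rate: "12% of patients in the usual care arm will continue statin therapy, which we consider a cautious estimate". No source is given.
- Contamination: "However, we anticipate that some contamination bias may occur", with the direction stated: "This could lead to a higher proportion of patients in the usual care arm choosing to continue treatment".
- Other inputs: two-sided alpha 0.05, 80% power, 2:1 allocation, 25% drop-out, 247 required, 249 funded and planned.

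The Data analysis plan says outcome values are not imputed, so drop-outs leave the primary comparison. The Study design section adds that "All HCPs who participate in this study will be trained to provide information on the nocebo effect to study participants", and that usual-care professionals discuss nocebo, promote statin use, and either attempt a rechallenge or prescribe another lipid-lowering drug.

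**The concern.** Two statements in the section do not fit the calculation they describe.

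First, the text claims a conservative basis of 29% and the calculation uses 30%. The difference is one point, in the direction that favours power, in a sentence whose purpose is to claim caution.

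Second, 12% is called cautious. When the intervention is expected to raise statin use, a low control rate widens the assumed difference and is therefore the optimistic choice. The section then says contamination may raise that rate, but the only allowance it states is the drop-out margin.

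At stake is how a null result would be read. If usual care ends a few points above 12% and the intervention arm is near the assumed value, the chance of missing a real difference is well above the 20% that the section implies.

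**Working it through.** **Inputs.** From the protocol article: 30% (used) and 29% (stated bound) for the intervention; 12% for usual care; 2:1; two-sided 0.05; 80% power; 25% drop-out; 249 randomised. Assumed, because the documents give no figures: usual-care rates of 13% to 15%, and an intervention rate of 35%.

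**Formula.** Two proportions, pooled variance under the null, no continuity correction. With control size n and intervention size 2n, p̄ = (p_c + 2p_t)/3 and

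n = [1.96 √(1.5 p̄(1 − p̄)) + 0.8416 √(p_c(1 − p_c) + p_t(1 − p_t)/2)]² / (p_t − p_c)²

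**Step 1: reproduce 247.** For 30% vs 12%, p̄ = (0.12 + 0.60)/3 = 0.24.
n = (1.0252 + 0.3862)² / 0.18² = 1.992/0.0324 = 61.5.
Total = 3 × 61.5 = 184.5, so 185. Then 185/0.75 = 246.7, so 247. This matches.

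**Step 2: the same at 29%.** p̄ = (0.12 + 0.58)/3 = 0.2333.
n = (1.0153 + 0.3843)² / 0.17² = 1.959/0.0289 = 67.8, so 68 + 136 = 204 evaluable. Then 204/0.75 = 272 randomised, 23 more than the planned 249. So 30% was the input.

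**Step 3: power at the planned size.** Evaluable = 249 × 0.75 = 186.75, split 62.25 and 124.5. Power = Φ[(p_t − p_c − 1.96 SE₀)/SE₁], where SE₀ uses p̄ and SE₁ the separate rates.

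- 30% vs 12%: SE₀ = 0.0663, SE₁ = 0.0582; (0.18 − 0.130)/0.0582 = 0.86; power 80.5%.
- 29% vs 12%: SE₀ = 0.0657, SE₁ = 0.0579; (0.17 − 0.129)/0.0579 = 0.71; power 76.2%.

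Exact enumeration of the chi-square test at 62 and 124 gives 81.7% and 77.6%; at 62 and 125 it gives 81.1% and 76.9%. The gap of about 4 points is the same.

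**Step 4: vary both rates** (same formula and evaluable numbers).

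| Usual care | Intervention 29% | Intervention 30% | Intervention 35% (assumed) |
|---|---|---|---|
| 12% (plan) | 76% | 81% | 94% |
| 13% (assumed) | 70% | 75% | 92% |
| 14% (assumed) | 63% | 68% | 88% |
| 15% (assumed) | 56% | 62% | 84% |

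From 30% vs 12%, lowering the intervention rate by one point costs 80.5 − 76.2 = 4.3 points of power. Raising usual care by one point costs 80.5 − 74.7 = 5.8.

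**The case against.** The strongest reply is that nothing has been miscalculated. The section openly gives 30% as its input, 247 follows from it, and taking 30% for a 29% bound is probably rounding. Power is always conditional: 76% applies if the true rate equals the lowest lower limit among four studies and drop-out reaches the full 25%. With 20% or 15% drop-out (assumed), the same formula at 29% vs 12% gives about 79% or 82%. The Introduction reports that 50% to 65% chose to restart in two of these studies, so the intervention rate was set low on purpose. Contamination is disclosed, and 12% may already describe the nocebo-informed usual care set out under Study design.

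Most of this stands, and it rules out several stronger readings that a reader might infer:

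- *The sample size is an arithmetic error.* It is not; only the description of its basis differs from the input.
- *The plan ignores contamination.* It names the mechanism and the direction. What is absent is a stated allowance.
- *Power is really near 40%.* At an assumed 18% in usual care, power is 42% with 30% in the intervention arm and 36% with 29%. No document gives 18%, and that scenario moves only the unfavourable input.
- *The 29% bound is not conservative, because the earlier studies counted willingness to restart as well as restarting.* How far that exceeds use at 12 months cannot be judged from this document, and 30% is already well below 50% to 65%.
- *The comparator must be relabelled.* Its content and the training are already described; a new label is a preference.

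The reply does not remove the mismatch between stated basis and input. Nor does it settle what 12% includes: the word that opens the contamination sentence, and the reference to a higher proportion, suggest an effect on top of 12%, but the text is ambiguous.

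**Conclusion.** The point holds as one of stated basis and missing sensitivity. On the basis that the section claims (29% vs 12%), the planned 249 give about 76% power. On the input it used (30% vs 12%), they give 80.5%. The larger uncertainty is the usual-care rate: at assumed values of 13% to 15%, power is about 75% to 62% with 30% in the intervention arm, and 70% to 56% with 29%.

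These figures assume 25% drop-out, unimputed outcomes and the pooled two-proportion formula that reproduces 247. They do not show that the trial is underpowered: if the true intervention rate were 35%, power would be about 84% even with 15% in usual care. They show that the 80% is sensitive to inputs that the section describes as conservative and cautious, and that the second description points the wrong way for power.

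**What to change.** Keep 249 and revise the section's wording:

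1. Either present 30% as the planning assumption and drop the claim that it is the lower bound, or restate power as about 76% at 29% vs 12%.
2. Say whether 12% already includes the expected contamination.
3. Replace cautious as the description of 12%.
4. Add a short two-way power table over intervention and usual-care rates, like the one above, with rates beyond the plan's own labelled as assumptions.

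No extra patients are needed, and the design and analysis do not change. The cost is a less favourable stated power.

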### Data analysis plan

For our primary endpoint, the percentage of patients that continue their statin will be analysed by calculating an odds ratio that compares the participants randomised in the intervention and usual care arm and by calculating its associated 95% CI. Secondary endpoints will be analysed by applying the same strategy as for the primary endpoint with regard to categorical variables. For continuous variables, differences will be reported with a mean (SD) or median (IQR) depending on the distribution of the data and differences will be tested using a t-test or Mann-Whitney U test. For the cost-effectiveness analysis, an empirical cost-effectiveness analysis (CEA) and cost-utility analysis (CUA) will be conducted, which will employ seemingly unrelated regression equations (SURE), adjusted for baseline scores, baseline costs and quality of life.

In the case of missing baseline data, data will be imputed on the basis of other baseline characteristics like age, sex, Body Mass Index (BMI) and history of ASCVD. As convention, the outcome and follow-up values are not imputed. Spurious data will be cleaned from the dataset.

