### Study design

The study comprises a randomised controlled trial (RCT) that is conducted in different (university) hospitals in the Netherlands. The study has two treatment arms in the first half year of the study: an arm in which participants will undergo an N=1-intervention and an arm in which they will receive usual care. The randomisation between these two arms is open-label and participants are randomised among those arms in a 2:1 ratio respectively. A 2:1 randomisation ratio ensures that the majority of participants receive the N=1 intervention, allowing for better-powered analyses for outcomes in which patients identified through the intervention as intolerant due to statin therapy or intolerant due to misattribution and/or nocebo effects are compared with each other. The randomisation will be stratified on study site and the use of ezetimibe at baseline and is performed in the data management system of the study. An overview of this study can be found in figure 1. Inclusions for this study began in April 2025, and we anticipate that the final participant will complete their last visit by December 2032.

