### Study population

Our study population will consist out of adult patients at high risk of ASCVD based on having FH or at very high risk based on having a diagnosis of previous ASCVD. All patients eligible for inclusion reported statin-related side effects while on ≥2 statins. The study will be conducted in at least 11 hospitals in The Netherlands, of which the academic medical centre of the Erasmus MC is the coordinating centre. Exclusion criteria for this study are:

a contra-indication for statin therapy;any condition that causes severe chronic muscle pain (ie, myopathy or myositis);a history of severe mental illness;a history of liver cirrhosis or severe renal insufficiency;an ASCVD event in the past 3 months;an inability or insufficiency to fill in the digital questionnaires;a clinical judgement of the HCP that LLT cannot be withheld in a patient with a recent ASCVD event in the past 12 months;the clinical judgement of the HCP that LLT is no longer relevant for the prognosis of the patient;the clinical judgement of the HCP that participation in the study is unethical or unwanted.

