### Planned outcomes

The primary outcome of the study is the incidence of self-reported statin use at 12 months after randomisation, which is a binary outcome measure (yes/no). We specifically chose this outcome as the primary endpoint because the main objective of the study is to determine whether N=1-interventions, compared with usual care, can increase statin use in patients in routine clinical practice. We considered the 12-month timepoint to be the most appropriate to evaluate this outcome, as we believe this timepoint, approximately 6 months after completion of the N=1-intervention, best reflects patients’ willingness to continue statin therapy in the longer term, beyond the immediate influence of the intervention. Secondary outcomes of this study are focused on use of cholesterol-lowering medication at different timepoints, cholesterol levels at different timepoints, cost-effectiveness, satisfaction with medication and multiple outcomes that assess the applicability of N=1-interventions in clinical care. All secondary outcomes that are studied are:

statin use;PCSK9i use;LDL-C levels;quality of life (EQ-5D-5L questionnaire);reported symptoms;cost-effectiveness (iMCQ and iPCQ questionnaire, among others);views on medication (BMQ questionnaire);satisfaction with statins (PESaM questionnaire);decisional conflict (DCS questionnaire);trust in the HCP (WFPTS questionnaire);HCP satisfaction with intervention (self-made, non-validated questionnaire with statements about acceptability on a 5-point Likert-scale; disagree-agree);treatment concordance during intervention;physical and mental complaints during intervention.

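### Randomisation is stratified by site and baseline ezetimibe use, but the primary odds ratio as stated uses neither, so power may be forgone if these factors predict statin use

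*Protocol article*

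**What the plan says.** - **Design** (Protocol article, Study design): "The randomisation will be stratified on study site and the use of ezetimibe at baseline". Allocation is 2:1 in favour of the N=1-intervention.
- **Sites** (Study population): "The study will be conducted in at least 11 hospitals in The Netherlands". With ezetimibe yes/no, that makes at least 22 strata.
- **Primary analysis** (Data analysis plan): the binary 12-month outcome is analysed by "calculating an odds ratio that compares the participants randomised in the intervention and usual care arm" and "by calculating its associated 95% CI". No covariate or stratum is named. Categorical secondary outcomes follow the same strategy. Continuous ones are compared by t-test or Mann-Whitney U test.
- **Adjustment elsewhere** (same section): the cost-effectiveness regressions are "adjusted for baseline scores, baseline costs and quality of life".
- **Planning assumption** (Sample size calculation): "30% of patients will continue using statins after the N=1-intervention compared with 12% in the usual care group", with 25% drop-out, two-sided alpha 0.05 and 80% power, giving 247 needed and 249 funded.

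**The concern.** Stratified randomisation forces the arms to be alike on site and ezetimibe use. If those factors predict the outcome, the true sampling variation of the arm comparison shrinks. An analysis that ignores them still counts the between-stratum variation as error, so it is conservative and does not collect the power that the design makes available.

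The article gives reasons to expect site to matter. Individual results are discussed in a consultation with the treating professional. Statin type and dose are left to that professional, as is the choice in usual care between rechallenge and another lipid-lowering drug. Sites include regional and academic hospitals. The sample-size section itself expects physicians' communication to shift usual-care uptake. With only two participants above the calculated requirement, a gain of a few points at no recruitment cost would be worth having.

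**Working it through.** **1. Reproduce the plan's figure.** Inputs from the Sample size calculation: p0 = 0.12, p1 = 0.30, ratio 2:1, two-sided alpha 0.05, 80% power, 25% drop-out. The pooled proportion is (0.12 + 2 × 0.30)/3 = 0.24.

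n0 = [1.960·√(1.5 × 0.24 × 0.76) + 0.842·√(0.12 × 0.88 + 0.30 × 0.70/2)]² / 0.18² = (1.025 + 0.386)² / 0.0324 ≈ 61.5

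This rounds to 62 controls, and 2 × 61.5 rounds to 123 intervention participants, 185 in all. 185/0.75 = 246.7, so 247. The figure reproduces, and the formula contains no stratum or covariate.

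**2. Power without adjustment.** 249 × 0.75 = 186.75, about 187 evaluable. The same formula gives 80.5%.

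**3. What the stratification factors could add.** The article does not say how strongly they predict 12-month statin use, so a range is assumed. Simulation: 2,500 trials per row, 249 enrolled, 25% random drop-out, 11 equally likely sites, 50% ezetimibe use, 2:1 blocks of three within strata, marginal rates held at 30% and 12%, Wald tests for the logistic models. Block size, site sizes and ezetimibe prevalence are also assumptions. Monte Carlo error on power is about 0.8 points.

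| Site SD (log-odds) / ezetimibe OR | Power: unadjusted | Power: logistic, ezetimibe + site | Power: Mantel-Haenszel, 22 strata | Coverage of unadjusted 95% CI | Type I error: unadjusted / logistic | Median SE of log OR: unadjusted / logistic |
|---|---|---|---|---|---|---|
| 0 / 1.0 | 80.0% | 81.0% | 79.0% | 96.0% | 4.2% / 4.9% | 0.442 / 0.455 |
| 0.3 / 1.5 | 79.8% | 81.7% | 79.6% | 96.2% | 4.8% / 5.4% | 0.442 / 0.459 |
| 0.5 / 2 | 81.5% | 83.8% | 82.5% | 96.8% | 4.1% / 4.8% | 0.444 / 0.470 |
| 0.8 / 3 | 81.3% | 86.8% | 85.6% | 96.6% | 3.6% / 5.0% | 0.445 / 0.495 |
| 1.0 / 4 | 81.4% | 87.4% | 86.4% | 97.2% | 3.1% / 4.9% | 0.445 / 0.516 |

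Coverage is for the marginal odds ratio, (0.30/0.70)/(0.12/0.88) = 3.14. In the first row nothing is prognostic, yet coverage is already 96.0% and type I error 4.2%. That much belongs to the Wald interval at this sample size. Only the drift down the table reflects the ignored factors.

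**4. Separate the test from the stratification.** Part of any gap between an unadjusted Wald test and a Mantel-Haenszel test arises because the latter is a score test. With strong factors and a 12% null rate, type I error was 3.1% for the unadjusted Wald test, 4.0% for the unadjusted score test and 5.0% for Mantel-Haenszel. Against an unadjusted score test, logistic adjustment gains about 0 to 2 points of power for weak or moderate factors and about 5 for strong ones. Mantel-Haenszel over 22 strata can lose 1 to 2 points when nothing is prognostic.

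**5. Sparseness.** 187/22 = 8.5 evaluable per stratum. About a third are controls (2.8), with 2.8 × 0.12 ≈ 0.3 control events per stratum. Expected events in total are 125 × 0.30 + 62 × 0.12 ≈ 45, against 12 coefficients (treatment, ezetimibe, ten site indicators), or 3.7 to 3.8 each. The cost shows in the first row: the true log odds ratio is ln 3.14 = 1.145, and the median estimate was 1.163 unadjusted but 1.235 with site indicators. So the 1-point gain in that row is not real efficiency.

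**The case against.** The strongest objection is that lack of adjustment is inferred from silence. The article never calls the odds ratio crude, an adjusted odds ratio would also fit the sentence, and covariates are often left to a full protocol or analysis plan that is not shown. This stands in part. Against it, the section does name adjustment where it is meant (cost-effectiveness), the tests named for continuous outcomes carry no covariates, and the sample size comes from an unadjusted formula. The fair statement is that the analysis as described uses neither factor.

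A reader might also infer three stronger things that the documents do not support:

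- **That the confidence interval is too wide.** Over-coverage of the marginal odds ratio is real but modest. Because the odds ratio is non-collapsible, adjustment gives a larger standard error on the log scale (0.455 to 0.516 against about 0.44), while the conditional estimate moves away from 1. The gain is in power, not in a narrower interval.
- **That planned power is lost.** 247 was calculated for an unadjusted comparison, and 249 delivers 80.5%. Only additional power is forgone.
- **That the loss is certain.** It depends on prognostic strength, for which the article gives no figure, and it vanishes if the factors do not predict statin use.

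It is also fair to say that the remedy has a price, since the strata are sparse and small sites need a rule.

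**Conclusion.** The point holds as an efficiency improvement that should be made. The plan as described does not analyse by the factors it randomises by. Validity is unaffected: the unadjusted type I error was 3.1% to 4.8% in every scenario, and the planned 80% is met. What is at stake is about 0 to 2 points of power if site and ezetimibe use are weak or moderate predictors and about 4 to 6 if they are strong, with unadjusted coverage of about 96% to 97%. These sizes rest on assumed prognostic strength, site sizes, ezetimibe prevalence and block size. The mismatch itself is clear from the text, subject to an unseen analysis plan that may already name the factors.

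**What to change.** State that the primary odds ratio comes from logistic regression of 12-month statin use on arm, baseline ezetimibe use and site. Fix a rule in advance for small sites, either pooling below a set size or a random site intercept. The small-sample shift seen with a full set of site indicators is a reason to settle this beforehand; the random-intercept version was not simulated here. Prefer this to Mantel-Haenszel over 22 or more sparse strata.

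Say that the result is a conditional odds ratio, or standardise it to a marginal one. Adjust the categorical secondary outcomes in the same way. If the full analysis plan already does this, confirm it and keep later descriptions consistent with it.

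The cost is wording, since both factors are already used in the randomisation. The downsides are the small-site rule and a conditional odds ratio that differs from the unadjusted one and has a larger log-scale standard error.

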
**Table 1 T1:** Treatment sequences in N=1-intervention arm of the study

Treatment sequence	Treatment period				Study results period
	1	2	3	4	
Sequence 1	S	P	S	P	S
Sequence 2	P	S	P	S	S
Sequence 3	P	S	S	P	S

S, statin; P, placebo.

During this fifth treatment period, participants will receive counselling on their individually reported symptoms and cholesterol levels during the treatment periods. They will receive a generated report consisting of several figures and graphs, which will among other things show the number of (muscle) symptoms during statin vs placebo periods, cholesterol levels across the different periods, the distribution of symptoms across different body regions and the extent to which symptoms affected their daily functioning, including any differences between statin and placebo periods. In addition, participants will receive a video that further explains their personal results. Subsequently, they will discuss their individual results in a consultation of approximately 30 min with their treating HCP. During this consultation, the results will be reviewed in detail and further interpretation will be provided, including whether the findings are suggestive of statin-attributable symptoms or symptom misattribution and nocebo effects. A 10 mm higher VAS during statin use is considered as the threshold to attribute the symptoms to statin use.^18 19^ After counselling, statin continuation is advocated if symptoms cannot be attributed to the statin, but it is voluntary and at the discretion of the participant. Participants will be treated according to the clinical guideline and prescribed a PCSK9i if necessary.

In the usual care arm of the study, participants will be treated according to the national cardiovascular risk management (CVRM) guidelines and reimbursement criteria for PCSK9 inhibitors.^20^ When patients with Familial Hypercholesterolaemia (FH) and/or ASCVD report side effects to at least three statins, they are considered statin intolerant as according to Dutch criteria and they qualify for reimbursement of PCSK9i.^21^ At the start of the intervention period, the HCP will discuss the prevalence of SAMS and the strong association with the nocebo effect as this is also stated in the international guidelines on cardiovascular disease prevention.^22^ The HCP will advocate statin use and attempt to rechallenge the patient with a statin or will prescribe another form of LLT, for example, a PCSK9i.

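### PCSK9i use at follow-up is compared by an odds ratio with no stated adjustment for PCSK9i use at baseline: valid under randomisation, but possibly inefficient

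*Protocol article*

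**What the plan says.** The Data analysis plan sets the primary analysis as "calculating an odds ratio that compares the participants randomised in the intervention and usual care arm", with its 95% confidence interval. It then extends this: "Secondary endpoints will be analysed by applying the same strategy as for the primary endpoint with regard to categorical variables". Planned outcomes lists PCSK9i use among the secondary outcomes, so as a yes/no variable it falls under that sentence. Baseline adjustment is described in the same section only for the cost-effectiveness analysis.

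Three other parts of the article bear on this:

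- **Study population** admits patients with familial hypercholesterolaemia or previous ASCVD who had side effects on two or more statins. None of the printed exclusions concerns current PCSK9i treatment.
- **Study design** (usual care arm) notes that such patients with side effects on three or more statins count as statin intolerant under Dutch criteria and that "they qualify for reimbursement of PCSK9i".
- **Study design** (randomisation): "The randomisation will be stratified on study site and the use of ezetimibe at baseline". PCSK9i use is not a stratification factor.

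Measurements and data collection includes self-reported medication use and pharmacy dispensing data.

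**The concern.** Some participants may already be on a PCSK9i when randomised: the criteria allow it, and part of the eligible population already qualifies for reimbursement. Anyone who enters on the drug and stays on it counts as a user at follow-up whichever arm they are in. Such patients add events equally to both arms, pull the overall odds ratio towards 1 and add variability that a baseline-adjusted analysis would remove. A chance imbalance in baseline use would also pass into the estimate unadjusted.

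The outcome matters because the Introduction motivates the trial partly by reducing reliance on costlier alternatives to statins, and PCSK9i use measures this directly. What is at stake is the precision of one secondary comparison.

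**Working it through.** **1. The plan's own sample size, to fix the evaluable numbers.** Sample size calculation gives the inputs: "Based on a two-sided alpha level of 0.05 and 80% power"; "30% of patients will continue using statins after the N=1-intervention compared with 12% in the usual care group"; a 25% drop-out margin; and "a total of 247 participants are needed for the study that has a 2:1 ratio".

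With pooled variance, no continuity correction and 2:1 allocation, the mean rate is (0.12 + 2 × 0.30)/3 = 0.24, and the control arm needs

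n = [1.96 × √(1.5 × 0.24 × 0.76) + 0.8416 × √(0.12 × 0.88 + 0.30 × 0.70/2)]² / 0.18²
= [1.0252 + 0.3862]² / 0.0324 ≈ 61.5, so 62.

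That is 62 + 124 = 186 evaluable patients, and 186/0.75 = 248 (245.9 without rounding), against 247 stated. The plan's figure is reproduced and is not in question here. I use 62 usual care and 124 N=1 patients below.

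**2. Assumptions for PCSK9i use.** The document gives no rates and no power target for this outcome, so the following are assumed:

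- Patients not on a PCSK9i at entry: 35% use one at follow-up in usual care, 15% in the N=1 arm.
- Patients on a PCSK9i at entry: either 95% still use it in both arms (strong persistence), or 70% in usual care and 50% in the N=1 arm (weak persistence).
- Baseline share b varied from 0% to 40%.

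**3. What the unadjusted comparison sees.** Under strong persistence the rate in an arm is 0.95b + (1 − b)r, where r is the non-user rate. At b = 0.20:

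- usual care: 0.19 + 0.28 = 0.47
- N=1: 0.19 + 0.12 = 0.31
- unadjusted odds ratio: (0.31/0.69)/(0.47/0.53) = 0.51
- odds ratio among non-users: (0.15/0.85)/(0.35/0.65) = 0.33

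**4. Power.** Simulation with 20,000 runs per cell, two-sided 5% level, comparing the unadjusted Wald odds ratio with a Mantel-Haenszel test stratified by baseline use:

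| Baseline users | Strong persistence: unadjusted → stratified | Gain (points) | Weak persistence: unadjusted → stratified | Gain (points) |
|---|---|---|---|---|
| 0% | 86% → 86% | nil | 86% → 87% | nil |
| 5% | 79% → 85% | 6 | 85% → 86% | 1 |
| 10% | 71% → 82% | 11 | 83% → 86% | 3 |
| 20% | 56% → 76% | 20 | 80% → 84% | 4 |
| 40% | 34% → 60% | 26 | 76% → 82% | 6 |

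At 0% the two methods are the same comparison; the half-point difference is between two test statistics. Separate simulations of the strong-persistence case gave gains within about 2 points of these: 10 at 10%, 19 at 20%, 28 at 40%. With no effect in either stratum, both methods rejected in about 5% of runs.

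**5. Other assumed rates.** With non-user rates of 40% and 20% and 95% persistence, power goes from 75% to 80% at 5% baseline users, from 68% to 77% at 10%, and from 44% to 62% at 30%. The pattern is the same.

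**6. What adjustment cannot recover.** In the strong-persistence column even the stratified analysis falls from 86% to 60%. That part of the loss comes from having fewer patients whose status can change.

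**7. Chance imbalance.** At b = 0.20 the standard deviation of the between-arm difference in baseline share is √(0.16 × (1/62 + 1/124)) = 0.062, so a difference of 10 points or more arises in about 10% of trials. At b = 0.40 it is about 19%.

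**The case against.** Four objections deserve an answer.

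**Baseline use is not shown.** Nothing in the article says that any participant is on a PCSK9i at entry. Qualifying for reimbursement is not the same as taking the drug, and entry requires only two failed statins while reimbursement requires three. The description of both arms fits patients for whom the PCSK9i decision still lies ahead. This stands. A reader might infer that the plan throws away much of the power for this outcome. That needs both a sizeable baseline share and high persistence, and the document supplies neither. Since lower reliance on PCSK9i is a hoped-for result, equal 95% persistence in both arms is itself open to doubt.

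**The word unadjusted is an inference.** The article condenses a fuller protocol, and an analysis plan may name covariates. This stands in part. The published text does commit to an odds ratio between arms and mentions baseline adjustment only for the cost-effectiveness analysis, so an unadjusted odds ratio is the natural reading. If a fuller plan already adjusts for baseline PCSK9i use, the point falls away.

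**Nothing is invalid.** Randomisation protects the unadjusted comparison, its confidence interval allows for chance imbalance, and a whole-population odds ratio is a legitimate target that differs from one conditional on baseline use. This stands fully. A reader might infer bias or an inflated error rate from the missing stratification; neither follows, and the simulated error rate is about 5% for both methods.

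**The cost argument is already adjusted.** The cost-effectiveness analysis accounts for baseline costs. This stands too, and confines the point to the clinical comparison of PCSK9i use.

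**Conclusion.** The point holds as an efficiency improvement to one secondary outcome. The article states no adjustment for baseline PCSK9i use, while its entry criteria and stratification leave that use uncontrolled.

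The benefit of accounting for it runs from nil (no baseline users), through about 1 to 6 points of power (weak persistence), to roughly 6 points at a 5% share and 26 to 28 at a 40% share (95% persistence). All of these rest on assumed PCSK9i rates and on 62 against 124 evaluable patients. The document cannot say where in this range the trial will fall.

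It may be tempting to carry the covariate into every model. For the primary outcome the calculated gain is only from 80% to 81–82%, and for LDL-C no gain has been calculated, so neither extension is supported as needed here.

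**What to change.** Prespecify, before outcome data are seen by arm, that PCSK9i use at each follow-up time is analysed by logistic regression with treatment arm and baseline PCSK9i use (yes/no) as terms, or by a Mantel-Haenszel odds ratio stratified by baseline use. Derive baseline use from the self-reported medication and pharmacy dispensing data. Report the unadjusted odds ratio descriptively beside it, and state that the adjusted odds ratio is conditional on baseline use, so the two need not agree even with perfectly balanced arms. Tabulate baseline PCSK9i use by arm so that readers can judge how much the adjustment matters.

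The cost is a sentence or two in the analysis plan and one covariate from data the trial already collects. Eligibility, randomisation, sample size and the primary analysis stay as they are. If baseline use proves rare, almost nothing is lost by having specified it.
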